### Study Aim and Objectives

In this study, we present the protocol for a 31-month SW-CRT trial. Our aim is to evaluate the performance of the SurgeCon platform in improving important patient and service process outcomes in EDs in an RHA in Newfoundland and Labrador and develop strategies to promote its scalability, sustainability, and successful implementation across the Canadian health system. The primary objective of the trial is to evaluate the effects of SurgeCon on ED performance by assessing its impact on LOS, PIA, and LWBS. The secondary objective of the trial is to assess the intervention’s impact on patient satisfaction and patient-reported experience with ED wait times and its ability to create better-value ED services by reducing ED costs.

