### Study Setting

Newfoundland and Labrador’s health care system is delivered through four RHAs: EH, Central Health, Western Health, and Labrador-Grenfell Health. The eastern RHA will be participating in this research initiative as a collaborative research partner and will be the only RHA participating in the study. The other 3 health authorities will act as knowledge users and will not be included in the SurgeCon trial. However, the research team will provide interim reports to the other health authorities to allow them to monitor and learn from research findings over the course of the study period to guide future implementation in their own centers.

This is a multisite study, including 2 urban and 2 rural EDs with 24/7 on-site physician support in the EH region of Newfoundland (Figure 1). The remaining 2 EDs with 24/7 on-site physician support within the study area that are not receiving the intervention are a pediatric ED, which operates differently and has wait times that differ greatly from adult or general ED, and the Carbonear General Hospital, which was chosen for the pilot study. The 4 sites receiving the intervention include 2 urban sites (Health Sciences Centre and St. Clare’s Mercy Hospital) and 2 rural sites (Dr. G.B. Cross Memorial Hospital and Burin Peninsula Health Care Centre).

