### Site Randomization

As we will be evaluating the effectiveness of SurgeCon using an SW-CRT, the 4 different hospitals will be randomized, with 1 ED site starting at the first sequence. The next site will start 6 months later in the second sequence and will continue until all EDs are allocated to sequences. A simple random sample will be performed by the study statistician, who will generate a randomization list using statistical software that will determine the order of intervention implementation. The researchers and participants will not be blinded to whether they are in the intervention or the control cohort.

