**Figure 2 figure2:**
[figure not shown]
Schematic representation of a SW-CRT with 4 steps for a 31-month study period. 
SW-CRT: stepped wedge cluster randomized trial.

The advantages of the SW-CRT include logistical flexibilities, efficiencies in terms of power, and sample size compared with traditional (clustered) parallel-group designs. Furthermore, the ethical advantages in longitudinal and open cohort studies have also been recognized [27-29]. A simple random sampling technique will be used to determine the order of intervention implementation across the 4 selected sites. The assignment of 1 cluster per sequence will maximize statistical power. The study period can be subdivided by four 6-month steps. Each step starts with the implementation of the intervention at one of the 4 selected sites. Observations are collected repeatedly from each cluster in multiple periods. The key parameters such as the number of clusters or clusters per sequence, steps, and measurement periods (both control and intervention conditions), intracluster correlation coefficient (ICC), and effect size are required for sample size calculation for the SW-CRT design.

The total study period available for the intervention to remain active is 31 months, and it is expected that at least one month will be needed for training and implementation at each ED site. A 1-month intervention adoption period was considered to be sufficient for the intervention to be fully operationalized for a single cluster. During the first 6 months of the baseline period, all patients who visit any of the 4 hospitals will receive usual care. After the baseline period, a randomly allocated hospital will begin SurgeCon intervention implementation every 6 months and will continue to use the intervention for operations and management until the end of the study. Staff at each of the randomly selected hospitals will undergo training, establish processes and guidelines that are consistent with efficiency principles covered during training, and begin routine data entry. During the last 6 months of the study period, all 4 hospitals will be operating using the SurgeCon ED management platform exclusively. We will be monitoring the characteristics of each hospital and the composition of their associated frontline teams to determine if significant changes have occurred since the control period and whether an adjustment to our analysis plan is required.

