Patient-reported experiences and patient satisfaction survey data will be collected 3 to 5 days after ED discharge via a telephone interview conducted by a research assistant who is also an EH employee. No identifiable information related to their ED visit will be collected during the survey, and patient consent will be obtained before the interview through an implied consent process that does not require a signed consent form. We provide all study participants with the opportunity to request an informed consent document that can be provided by email or post mail and contains contact information for the principal investigator and project manager. To minimize the loss to follow-up, the research assistant will attempt to reach patients up to 3 times within 2 weeks of the initial attempt. The interview will take <30 minutes, using a questionnaire we created based on CIHI’s patient-reported experiences [38] and patient satisfaction surveys for EDs [39]. Although most of Newfoundland and Labrador’s population is English speaking (97%) [40], language was not considered an exclusion criterion. Patient interview responses will be stored via Qualtrics (a web-based survey program), where research team members will be able to analyze the data while maintaining patient anonymity. An important consideration for this approach is that the only ethically approved means of contacting patients is by telephone using patient contact information at EH. Other options were explored such as surveying patients directly in the ED, but it was deemed unsuitable, as many patients are not likely to be in a physical or mental state conducive to participating in a study.

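### The blanket statement that researchers are not blinded also covers the telephone interviewer who collects satisfaction and experience, leaving this subjective secondary outcome open to interviewer bias in the staggered rollout months

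*Protocol article*

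**What the plan says.** All places are in the protocol article.

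- **Study Aim and Objectives:** "The secondary objective of the trial is to assess the intervention’s impact on patient satisfaction and patient-reported experience with ED wait times". The outcome is subjective and secondary.
- **Data Collection and Monitoring:** the survey is done 3 to 5 days after discharge, "via a telephone interview conducted by a research assistant who is also an EH employee". The section explains the contact route: "the only ethically approved means of contacting patients is by telephone using patient contact information at EH". It adds that "No identifiable information related to their ED visit will be collected during the survey".
- **Site Randomization:** "The researchers and participants will not be blinded to whether they are in the intervention or the control cohort". No exception is made for anyone who collects outcome data.
- **Study Setting:** "The eastern RHA will be participating in this research initiative as a collaborative research partner". Eastern Health (EH) is also the only authority taking part.
- **Study Design (text below Figure 2):** "During the first 6 months of the baseline period, all patients who visit any of the 4 hospitals will receive usual care". One hospital then crosses over every 6 months. At the end, "During the last 6 months of the study period, all 4 hospitals will be operating using the SurgeCon ED management platform exclusively".
- **Statistical Analysis:** the individual-level model for satisfaction and experience has fixed effects for time, an intervention effect, and random cluster and cluster-by-time effects.

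**The concern.** In a stepped wedge trial the condition of a visit follows from two facts, the hospital and the date. ED staff cannot be kept unaware of a new way of running their department. The person who telephones patients afterwards is in a different position: nothing described about the interview requires that person to know where the hospital stands in the rollout.

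The outcome is a patient's opinion, obtained in conversation and recorded by the interviewer. If tone, prompting or recording differs even slightly between visits known to be under usual care and visits known to be under SurgeCon, the difference enters the treatment contrast. The interview is the only source described for this outcome, so no objective record could reveal the drift. At stake is a satisfaction result that favours SurgeCon without a matching change in what patients experienced.

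**Working it through.** **1. The plan's own figure.** The Sample Size section asks for 11 responses per month per hospital over 30 months and 4 hospitals: 11 × 30 × 4 = 1,320, as stated. The step from a 30% change to 11 per month cannot be reproduced, because no SD or baseline level is given. That figure is not in dispute; it serves only to set a scale.

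**2. When the condition can be hidden.** With a 6-month baseline and 6-month steps, the 30 months divide as follows:

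| Months | Hospitals on SurgeCon | Does the date alone reveal the condition? |
|---|---|---|
| 1–6 | 0 of 4 | yes |
| 7–24 | 1, 2, then 3 of 4 | no, the hospital is also needed |
| 25–30 | 4 of 4 | yes |

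Withholding the hospital can therefore mask the condition in at most 18 of 30 months (60%). In the other 12 (40%) the calendar gives it away.

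**3. When bias reaches the estimate.** Let X(i,t) = 1 if hospital i is on SurgeCon in month t, and let knowledge of the condition add b to every intervention score. Take a model with one effect per month.

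- *Bias only in the same-condition months.* It is 0 in months 1–6 and b for every hospital in months 25–30. That is a pure month effect, so it adds 0% of b to the intervention estimate.
- *Bias only in the staggered months.* It equals b·X(i,t) minus b in months 25–30. The second part is a month effect and the first is the treatment term, so 100% of b passes through.

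A numerical fit gives the same 0% and 100%. If time is instead a straight line, the split is about 5% and 95%.

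**4. Scale.** Inputs from the plan: I = 4 hospitals, T = 30 months, n = 11 per cell, ICC = 0.1. Assumptions: total SD = 1, a two-sided 5% test (sidedness is not stated), and the basic Hussey-Hughes model without random time effects.

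- σ² = (1 − 0.1)/11 = 0.0818; τ² = 0.1
- U = ΣX = 24 + 18 + 12 + 6 = 60
- W = Σ over months of (hospitals on SurgeCon)² = 6 × (1 + 4 + 9 + 16) = 180
- V = Σ over hospitals of (months on SurgeCon)² = 24² + 18² + 12² + 6² = 1,080
- Var = Iσ²(σ² + Tτ²) / [(IU − W)σ² + (U² + ITU − TW − IV)τ²]
- Numerator: 4 × 0.0818 × (0.0818 + 3) = 1.0086
- Denominator: (240 − 180) × 0.0818 + (3,600 + 7,200 − 5,400 − 4,320) × 0.1 = 4.909 + 108 = 112.909
- Var = 0.00893, so SE = 0.095 SD; detectable effect at 80% power = 2.80 × SE = 0.265 SD

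With no true effect and a bias b, the chance of a significant result is 1 − Φ(1.96 − b/SE) + Φ(−1.96 − b/SE):

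| Assumed b (SD) | b/SE | False-positive rate |
|---|---|---|
| 0 | 0 | 5% |
| 0.05 | 0.53 | 8% |
| 0.10 | 1.06 | 18% |
| 0.20 | 2.12 | 56% |

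The values of b are illustrations, not estimates. The random time effects in the planned model would enlarge the SE and so reduce these rates.

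**The case against.** The case on the other side has several parts.

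- **The article openly discloses the lack of blinding and contradicts nothing.** That is so. Disclosure still does not explain why the waiver extends to the interviewer. The telephone-only route with EH-held contact details plausibly explains an EH caller, but not a caller who knows the hospital's status. The anonymity wording protects patients and does not mask the assessor.
- **The interviewer's knowledge is inferred.** Data Collection and Monitoring does not say what the caller sees; the inference rests on the general sentence under Site Randomization. That sentence is categorical, so the inference is fair, but it remains an inference.
- **EH employment.** A reader might infer that employment by the rated authority biases the comparison in itself. It does not: the same employment applies in control and intervention periods, so a general wish to please is common to both. Employment matters only in combination with knowing the condition. Nor is EH the developer of SurgeCon; it runs the hospitals and partners in the research.
- **The script.** A reader might infer that patients hear of SurgeCon before answering, or that answers are freely probed and coded. The article says neither. It describes a questionnaire based on established experience and satisfaction surveys, and closed, neutral wording may already be in use.
- **Feasibility.** A reader might infer that masking would be easy. The documents do not show that. Patients talking about a visit may name the hospital, and a list prepared only once a month would break the 3 to 5 day interview window. This part of the objection stands, and it shapes the remedy.

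**Conclusion.** The point holds in a limited form. The plan waives blinding for all researchers without excepting the person who collects a subjective secondary outcome, and gives no reason for including that person. The exposure lies in the 18 staggered months, where a condition-related shift passes in full into the estimate if month effects are fitted (about 95% if time is linear). Partial masking is therefore worthwhile even though it cannot work in the other 12 months: it acts where the bias would count.

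The size of any bias cannot be derived from the documents. The rates of 8% to 56% show only that a modest shift would matter against an SE of about 0.095 SD, under the assumptions listed. LOS, PIA and LWBS come from administrative data and are not touched. This is a desirable improvement to a secondary outcome, not a threat to the trial's main result.

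**What to change.** 1. Under Site Randomization, limit the no-blinding statement to ED staff, patients and implementers.
2. Give the existing interviewer a call list pooled and shuffled across the 4 hospitals, refreshed every few days so that the 3 to 5 day window is kept, with hospital and rollout status withheld.
3. Have existing EH or data staff attach hospital and visit month by study number after the answers are recorded, within the approved EH contact route. The individual-level model needs cluster and time, so this supplies what the analysis requires.
4. Confirm that the questions are read in neutral, fixed wording that does not mention SurgeCon before the answers are recorded.
5. Have the interviewer record when a patient reveals the hospital.
6. Where masking is not feasible, say so and report the limitation. This includes the interviews already completed (570 by February 2022) if they were unmasked.

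**Cost.** The interviewer and the number of calls stay the same. List preparation and the later linkage take some extra staff work, and ethics may need to be notified. Masking remains partial, because patients may name their hospital and the calendar reveals the condition whenever all sites share it.

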### Statistical Analysis

#### Analyses

The characteristics of hospitals and patients will be recorded. We will describe the clinical and demographic characteristics of hospitals and patients for each period. We will report the response for patient satisfaction surveys and report the duration of intervention adherence at each study site and, if applicable, the reasons for noncompliance. For each outcome, we will report the results for each period, including the effect size and its precision. The 30 months of cumulatively collected data from EH and provincial health administrative databases in both the intervention and usual care periods will be modeled as a linear mixed model. We plan to analyze research data using a generalized linear mixed model (GLMM) [41] or generalized estimating equation [42]. Hussey and Hughes [43] have suggested a model-based approach for analyzing data using a repeated cross-sectional design where outcome measurements will be measured from different individuals at each measurement interval. This approach was proposed for continuous outcome variables and has been commonly used at the design stage of these studies [44]. Individuals within the same cluster are likely to be positively correlated, and the strength of the correlation can be measured by the ICC under this model and is assumed to be constant over time. However, the model suggested by Hussey and Hughes [43] has been extended to allow a more general correlation structure between individuals within the same cluster [45-47]. We will adhere to the intention-to-treat analysis; however, sensitivity analyses for comparing the results under the intention-to-treat assumption with the complier and per protocol will be conducted. Moreover, interim analyses will be conducted on a monthly basis to inform us about the findings in a timely manner and allow us to make any modifications if required [48].

The primary method of analysis used in this study is GLMM, which will consider monthly cluster-level summary measures such as means of LOS, PIA, or proportion of LWBS. Our GLMM models will include fixed effects for time, intervention effects, random effects, and random time effects for each cluster. In addition, ED setting (rural or urban), ED volume, and size of ED administrative resource will be added as cluster-level covariates. For secondary outcomes such as patient-reported experience and satisfaction, our individual-level GLMM models will include fixed effects for time, intervention effect, and random effects and random time effects for each cluster, with the covariates consisting of age, gender, the reason for ED visit, and cluster-level LOS, PIA, and proportion of LWBS.

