We have created a quality improvement intervention called SurgeCon. As a pragmatic ED management platform, SurgeCon includes 3 separate components (described below) that together act to decrease wait times and improve the sustainability of Newfoundland and Labrador’s ED services without significant workforce changes. These interventions include restructuring the ED organization and workflow, fostering a patient-centric environment, and quantifying ED demands and available resources in real time. SurgeCon is designed to enable frontline health care workers to anticipate and mitigate surges in patient volume through a series of proactive steps and decision-making tools. SurgeCon attracted the attention of the Newfoundland and Labrador Eastern Health (EH) RHA after they missed their own ED wait time benchmarks in 2016 [22]. The initial development of the SurgeCon intervention came about after an external review was completed by an independent third party to determine which areas of ED operations could be adjusted to improve wait times and departmental efficiency. The external review was one of many components included in a provincial wait time reduction initiative [23].

We piloted SurgeCon at the ED located in Carbonear, Newfoundland and Labrador, an EH administered hospital, over 45 months from July 1, 2013, to March 31, 2017. Data from the pilot study were analyzed using an interrupted time series analysis to assess its effect on ED performance. The resulting change in indicators was noteworthy, despite a 25.7% increase in patient volume. Over the course of the 45-month pilot study, average time to physician’s initial assessment (PIA) decreased from 104.3 (SD 9.9) minutes to 42.2 (SD 8.1) minutes, length of stay (LOS) in the ED decreased from 199.4 (SD 16.8) minutes to 134.4 (SD 14.5) minutes, and the number of patients LWBS decreased from 12.1% (SD 2.2%) to 4.6% (SD 1.7%). All of these changes were statistically significant. The marked and sustained impact of SurgeCon on ED performance in Carbonear supports the case for its extension to other EDs.

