### Data Collection and Monitoring

Aggregate- and individual record-level data will be analyzed over the course of the study period to assess the effect of the intervention on patient outcomes, health service efficiency, and the cost of providing emergency care. Our analysis will include aggregate KPI data, record-level health administrative data, and aggregate financial data and will be provided to the research team by the Newfoundland and Labrador Centre for Health Information. The ED KPIs (ie, LOS, PIA, and LWBS) used as the primary outcomes for this study are further described in Table S1 in Multimedia Appendix 1 alongside other variables that will be used for statistical modeling. Each of the primary outcomes will be calculated and assessed monthly over the course of the study period. The total number of monthly ED visits will be used as the denominator for our cluster-level summaries.

Individual record-level health administrative data will include demographic variables (eg, sex, date of birth, and postal code), mortality data, wait times data, diagnosis data, and triage acuity scores, among other variables. These data will be used to create aggregate KPI and financial data provided by Newfoundland and Labrador Centre for Health Information and to assess the intervention’s impact on the type and volume of patients who visit one of the 4 selected ED sites during the study period. Financial data will capture expenditures for staff, supplies, and procedures originating from the ED and will include data related to pharmacy, diagnostic imaging, laboratory testing, surgical day care, operating room procedures, physician salaries, physician fees for service claims, nurse salaries, administrative staff salaries, ambulance services, and other related ED costs.

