### Impact of COVID-19

The impact of the COVID-19 pandemic on the study and its protocol is ongoing. Public health care measures such as stay-at-home orders, handwashing, and physical and social distancing compounded with COVID-19 concerns have caused rapid disruptions in daily life and a delay in the implementation of the intervention. A notable effect may be a significant change in the number of patients visiting EDs. The fear that the public is experiencing because of COVID-19 is likely exacerbated by measures related to stay-at-home orders, self-isolation protocols, including quarantines, travel restrictions, and closures of nonessential businesses. With most of Newfoundland and Labrador’s residents practicing social distancing and self-isolating and an increase in the number of workers who are now working remotely, the potential for injuries such as trauma due to motor vehicle collisions may decline considerably [50]. Given the potential reduction in injury and the climate of fear at the beginning of the COVID-19 pandemic, patients were found to be less likely to use hospital ED services [51]. Another impact of the pandemic is the temporary suspension of essential and nonessential medical procedures. The suspension of certain health care services may have downstream effects on wait times because delays in surgeries and other important medical procedures could increase the number of higher acuity patients who develop complications because of the delay. These higher acuity patients require additional resources and time and can have a significant impact on patient flow and wait times. Other pandemic-related considerations include added wait times because of public health measures such as increased handwashing, social distancing, donning and doffing of personal protective equipment, and sanitizing high-touch surfaces. More recently, a transition from in-person to web-based or telephone family physician consultations may be increasing ED patient volumes [52,53]. The pandemic has also exacerbated issues related to physician and nursing shortages in the province [54-56]. As a result, achieving optimal sample size from each of the ED sites might be compromised because of pandemic-related ED service use trends. The research team will look to explore the effects of the COVID-19 pandemic on patient flow and wait times in EDs.

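### As written, the primary model for LOS, PIA and LWBS has no adjustment for patient mix, so a site-specific change in who attends that coincides with crossover would be read as a SurgeCon effect

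*Protocol article*

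**What the plan says.** Under Statistical Analysis (Analyses), the protocol article names a GLMM as the primary method, "which will consider monthly cluster-level summary measures such as means of LOS, PIA, or proportion of LWBS". On model terms it says: "Our GLMM models will include fixed effects for time, intervention effects, random effects, and random time effects for each cluster". It then lists the covariates: "In addition, ED setting (rural or urban), ED volume, and size of ED administrative resource will be added as cluster-level covariates". The individual-level model for patient experience and satisfaction, in the same paragraph, is treated differently, "with the covariates consisting of age, gender, the reason for ED visit, and cluster-level LOS, PIA, and proportion of LWBS".

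Data Collection and Monitoring says that record-level administrative data will hold "demographic variables (eg, sex, date of birth, and postal code") as well as "mortality data, wait times data, diagnosis data, and triage acuity scores, among other variables". The same section plans to assess whether the intervention affects the type and volume of patients attending. Impact of COVID-19 raises the possibility of more high-acuity patients after deferred care and adds: "These higher acuity patients require additional resources and time and can have a significant impact on patient flow and wait times". For ED visits, the Sample Size section mentions age, sex and acuity only as subgroup analyses.

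**The concern.** A stepped wedge estimate rests almost entirely on change within each site before and after its crossover. A covariate that is fixed within a site cannot account for such change. ED setting is fixed, and administrative-resource size plausibly nearly so. ED volume does move within a site (Background, on the pilot: "The resulting change in indicators was noteworthy, despite a 25.7% increase in patient volume"), but a count of visits does not say who the visitors were.

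If the share of high-acuity or older patients changes at a site around the time SurgeCon starts there, the raw monthly mean LOS changes even if no patient is treated faster or slower. If high-acuity visits last longer, a fall in their share looks like a benefit and a rise hides one. PIA and LWBS are exposed in the same way. The sign for PIA may differ, since Table 1 has unstable CTAS 1 and 2 patients treated immediately. At stake is whether a fall in LOS can be attributed to faster care. The data to check this are already collected, and the plan adjusts for patient characteristics in the secondary model but not in the primary one.

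**Working it through.** **The plan's own figures.** The LOS sample size multiplies out: 169 × 30 × 4 = 20,280. Its power basis cannot be reproduced, because no patient-level SD of LOS is given. The Sample Size section also cites a 10-minute reduction in LOS, which serves below only as a yardstick.

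**Layout.** 4 sites × 30 months (Study Design; Sample Size), with crossovers taken after months 6, 12, 18 and 24. The one-month adoption period is ignored. Site and month effects are fitted by least squares.

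**Step 1: can ED setting help?** Site effects, month effects and the intervention indicator give a design matrix of rank 34. Adding rural/urban leaves the rank at 34, so it adds nothing to the within-site contrast. With a random site intercept (ICC 0.1, 169 visits per site-month), the standard error of the effect is 0.0243 SD units with or without it.

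**Step 2: how does a mix change enter?** Let p be the shift in high-acuity share and g the LOS gap in minutes between high-acuity and other visits.

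- Shift starting at every site's crossover: bias = p × g, one for one.
- Shift at one site only, at its crossover: 0.20, 0.30, 0.30 or 0.20 of p × g, for the first to fourth site to cross.
- Shift common to all sites in calendar time: bias 0, because the month effects absorb it.

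**Step 3: illustrative size.** The documents give neither p nor g, so both are assumed. For a shift at every crossover:

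| Shift in share | g = 60 min | g = 120 min | g = 180 min |
|---|---|---|---|
| 2 points | 1.2 | 2.4 | 3.6 |
| 5 points | 3.0 | 6.0 | 9.0 |
| 10 points | 6.0 | 12.0 | 18.0 |

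For 5 to 10 points the range is 3 to 18 minutes. If only one site shifts, it is 3.0 × 0.20 = 0.6 to 18.0 × 0.30 = 5.4 minutes.

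**Step 4: a composition example.** Take the pilot's baseline LOS of 199.4 min and its 25.7% volume rise, and assume that all extra visits are low acuity, average L minutes and arrive at crossover. The new mean is (199.4 + 0.257 × L) / 1.257.

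- L = 100: 179.1, a fall of 20.3 min.
- L = 160: 191.3, a fall of 8.1 min.
- With 10% extra visits, the falls are 9.0 and 3.6 min.

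This is a worst case on timing and mix, and it leaves out the volume covariate.

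**Step 5: does ED volume rescue the estimate?** It depends on what ordinary monthly swings in volume carry. In trial runs of the L = 120, 25.7% case (assumed monthly volume CV 3 to 15%, residual SD 5 min), the false effect was about −16 min without volume. With log monthly volume it was about +1 min if ordinary swings are also low acuity, and about −17 to −18 min if they carry no mix change. Volume is therefore not a dependable substitute for mix.

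**The case against.** - **The variable list may be longer.** Data Collection and Monitoring points to Table S1 in the appendix, which is not shown, for other modelling variables. This stands. The point concerns the covariates written in the Analyses section and does not show that age and acuity are absent from every plan document.
- **The bias is conditional.** Site order is randomised, common shifts cancel, and random cluster-time effects put site-specific drift into the uncertainty. This stands as a limit on the claim. Those random effects do not remove a shift aligned with crossover, and four sites leave little averaging.
- **The pilot's 25.7% rise does not support an 8 to 20 minute bias.** A reader might infer that from Step 4. The protocol reports the rise over 45 months and attributes it neither to SurgeCon nor to low-acuity patients. With the rise spread over 18 months, the L = 120 case gave about −2 min instead of −16.
- **Precision.** A reader might also infer that leaving out acuity wastes precision. The documents give no basis for this. With an assumed R² of 15%, 1,000 to 3,000 visits per month and a site-month SD of 10 to 15 min, the standard error falls by about 0 to 1%. Keeping ED setting in the model does no material harm either.
- **The estimand.** The objective is service-level performance. If SurgeCon changes who attends, that belongs to its total effect. CTAS is also scored at a triage step that SurgeCon alters (Table 1). This stands, and it argues against making a CTAS-adjusted analysis the sole primary one.
- **A shift would be visible.** Patient characteristics will be described by period, and acuity subgroups are planned. Both help detection, but neither corrects the primary estimate.

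**Conclusion.** The point holds in a limited form. As the Analyses section is written, nothing in the primary model separates faster care from a site-specific change in patient mix at crossover, although the variables needed are held for every visit and the protocol itself says acuity can affect wait times. The effect on LOS could be negligible, or could reach or exceed the cited 10 minutes: 3 to 18 minutes for a 5 to 10 point shift at every crossover, and 0.6 to 5.4 minutes if only one site shifts. Both ranges rest on assumed shifts and LOS gaps. The documents do not show that such a shift will happen. They plan to assess the type and volume of patients, and they say only that higher acuity is possible after deferred care.

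**What to change.** In the Analyses section, keep the unadjusted GLMM and pre-specify two companions:

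1. The same GLMM adjusted for age and sex, either at visit level or on monthly outcomes standardised to the pooled baseline mix of the four sites.
2. A further version that adds CTAS, labelled as a sensitivity analysis because SurgeCon changes triage and may change who attends.

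Report age, sex and CTAS mix by site and period, and base any claim of faster care on agreement between these analyses. If Table S1 already provides for this, a cross-reference in the Analyses section is enough.

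The cost is wording and a modest amount of programming, with no new data. The adjusted estimates answer a narrower question, the effect at a fixed patient mix, and should be described that way.
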